### Interventions—adherence

In this trial adherence refers to the degree to which patients and IBD-team act in accordance with the flarometer advice. Low adherence can have a substantial effect on statistical power and interpretation of the trial results. To help avoid these potential detrimental effects of non-adherence, we have implemented the following procedures: (1) screening candidate participants for having an unfavourable disease course, as this may be a proxy for non-adherence; (2) reminding study participants automatically that the next flarometer score is due; (3) contacting non-responders by telephone after two weeks of passivity; (4) informing both patient and local IBD-team about the flarometer treatment advice; (5) documenting ignored red alerts (i.e. failing to intensify treatment despite flarometer score in high risk stratum); and (6) restricting the statistical analyses to those participants who replied to more than 80 % of the alerts to use the flarometer.

### Outcomes

The primary endpoint is the frequency of relapse rate during a 52-week follow-up period. Investigators, health providers and patients cannot be blinded to the assigned intervention. To minimize bias the primary endpoint is strictly defined as a clinical activity index score >10 points (see Table 1), necessitating steroid therapy, a six-week course of exclusive enteral nutrition, aminosalicylate dose escalation, or introduction of anti-TNF antibodies (infliximab or adalimumab). We will calculate Kaplan-Meier curves for both assignment groups. Time-to-relapse will be compared with a two-sided logrank test. The hazard ratio with its 95 % confidence interval for relapse will be provided with a Cox proportional hazards (multivariate) regression analysis. Potential confounding factors, including age at diagnosis, type of IBD, date of last relapse, emotional maturity and level of education, will be included in the Cox proportional hazards model.

**Table 1 Tab1:** Translation of clinical score systems to Physician’s Global Assessment

Physician Global Assessment	PCDAI [7]	shPCDAI [14, 38]	PUCAI [8]
Remission	<10	<10	<10
Mild activity	10-30	10-25	10-34
Moderate activity	≥30	26-40	35-64
Severe activity		>40	≥65

We are collecting data from a range of secondary endpoints, including the IMPACT-III score. This is a disease-specific quality of life score, composed of 35 items on 6 domains: IBD-related symptoms (7 items), systemic symptoms (3), emotional functioning (7), social functioning (12), body image (3) and treatment/intervention-related concerns (3) [25, 26]. Each item is scored on a 5 point Likert scale, coded from 0 to 4 points. Higher scores indicate better quality of life. The IMPACT questionnaire is validated for use in children eight years old and older and is recommended for the evaluation of new therapies because of its high sensitivity to change. The IMPACT-III (NL) is a translated and modified version of the original Canadian questionnaire that used a visual analogue scale [27, 28]. The Likert scale was introduced as it has been shown that children consider it easier to complete than a visual analogue scale [29]. To compare the difference of IMPACT-scores from baseline to final visit Student’s *t*-test or analysis of variance will be used where appropriate. Other secondary endpoints include the number of unscheduled health visits, hospital admissions, IBD-related absenteeism from school or parental work, and drug adherence, using the Morisky Medication Adherence Scale (Fig. 3) [30].

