**Methods/design:**

A randomized trial of web-based disease monitoring versus usual care is conducted at 10 Dutch IBD care centers. We plan to recruit 180 patients between 10- and 19-years old with quiescent IBD at baseline. Teenagers assigned to IBD-live will use the flarometer -an automatic cumulation of disease activity and fecal calprotectin measurements- to estimate probability of relapse. In case the flarometer indicates high risk the patient requires treatment intensification in accordance with national guidelines; low risk means that maintenance therapy is unchanged; and intermediate risk requires optimisation of drug adherence. Patients assigned to usual practice get the best accepted medical care with regular health checks. Primary outcome is the frequency of relapse at 52 weeks of follow-up. The diagnosis of relapse is based on a clinical activity index score >10 points necessitating remission induction therapy. Secondary outcomes include quality of life and cost-effectiveness.

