### Trial design

This trial is designed as a randomized, controlled, open label multicenter superiority strategy trial with two parallel groups. For allocation concealment, randomization will be carried out using a separate list of computer-generated random allocation numbers for each participating center (involving permuted blocks with a ratio of 1:1 allocation).

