### Randomization and masking

Eligible patients for whom consent or assent is provided will be allocated in a 1:1 ratio to the two arms of the study according to a computer-generated random sequence stratified by research site and disease type (Crohn’s disease vs. ulcerative colitis), and using blocks of variable size. The allocation sequence is generated by the biostatistics unit of the UMCG, and is not available to any member of the research team. Allocation concealment will be ensured, as the study website (https://www.ibd-live.nl) will not release the randomization code until the teenager has been recruited into the trial, which takes place after all baseline measurements have been completed. The nature of the intervention does not allow blinding of participants, care providers, or outcome assessors.

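### The log-rank test is stated without the randomization strata and the hazard ratio is adjusted differently, so p-value and interval can disagree; any power loss is small and depends on how prognostic the strata are

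*Protocol article*

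**What the plan says.** The Outcomes section of the protocol article names the primary test: "Time-to-relapse will be compared with a two-sided logrank test". It mentions no strata. The next sentence takes the effect estimate from a different model: "The hazard ratio with its 95 % confidence interval for relapse will be provided with a Cox proportional hazards (multivariate) regression analysis". The factors for that model are given as "including age at diagnosis, type of IBD, date of last relapse, emotional maturity and level of education, will be included in the Cox proportional hazards". Type of IBD is on the list and site is not, although the list opens with a word that leaves room for more.

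Randomization and masking says allocation is "stratified by research site and disease type (Crohn’s disease vs. ulcerative colitis), and using blocks of variable size". Trial design describes only "a separate list of computer-generated random allocation numbers for each participating center", with permuted blocks, and does not mention disease type. Statistical methods adds an interaction test by disease type, but no stratified primary test.

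**The concern.** Three things do not line up.

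- **Design and test.** Allocation is balanced within site and disease type, but the test as stated uses neither. Balance on a prognostic factor makes the real variability of the arm comparison smaller than the plain log-rank variance allows for. The test then rejects too rarely under no effect and gives up some power.
- **Test and estimate.** The log-rank p-value is marginal. The Cox hazard ratio is conditional on five covariates, only one of which is a randomization stratum. One can be significant while the other's 95% interval includes 1, and the article does not say which is decisive.
- **Two descriptions of the strata.** One list per center is not the same as one list per center and disease type. The analysis cannot be matched to the design until one description stands.

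**Working it through.** **Inputs from the article.** 90 per group with up to 10% loss; two-sided 5%; 1:1 allocation; 10 centers; 40% relapse against 25%. Those two rates are given for protocol versions 1 to 5. The current calculation states only a 15-point reduction, so carrying them forward is an assumption.

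**Inputs assumed.** The prognostic strength of site and disease type, and a 40% share of ulcerative colitis. The article gives neither.

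**Baseline power.** The article has no figure on stratification to reproduce, so its sample sizes were checked first.

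- Earlier binary design: n = [1.96·√(2·0.325·0.675) + 0.842·√(0.40·0.60 + 0.25·0.75)]² / 0.15² = 152 per group. This matches the article.
- Time-to-event: HR = ln(0.75)/ln(0.60) = 0.563. With 81 evaluable per group, events = 162 × 0.325 = 52.65. Power = Φ(√(52.65/4) × |ln 0.563| − 1.96) = about 55%.

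The stated 80% is therefore not reproduced at these rates. That is a separate sample-size matter. It explains why the powers below sit near 50%, and it is not caused by the missing strata.

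**Number of cells.** 10 centers ("usual care is conducted at 10 Dutch IBD care centers") × 2 disease types = 20 cells, and 180/20 = about 9 patients per cell.

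**Simulation 1.** 180 patients, 10 unequal sites, permuted blocks of 2 and 4 within site by disease type, 10% loss; 6000 runs under no effect and 4000 under HR 0.563. Each entry gives the test unstratified / stratified by disease type / stratified by site and disease type.

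| Assumed strength | Rejection under no effect, % | Power, % |
|---|---|---|
| Strata not prognostic | 5.3 / 5.4 / 5.4 | 56.0 / 55.8 / 54.1 |
| Site SD 0.3 (log hazard), disease HR 1.5 | 4.8 / 4.9 / 5.1 | 53.8 / 54.2 / 53.2 |
| Site SD 0.5, disease HR 2 | 4.3 / 4.6 / 5.3 | 50.1 / 51.6 / 53.4 |
| Site SD 0.8, disease HR 2.5 | 2.7 / 2.9 / 4.7 | 42.0 / 44.0 / 49.2 |

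Monte Carlo error is about 0.3 points for type I error and 0.8 for power. Only comparisons within a row are meaningful, because the assumed heterogeneity itself changes power from row to row. Stratifying by all 20 cells costs about 2 points when the strata carry no information (56.0 − 54.1 = 1.9) and gains about 7 when they are very strong (49.2 − 42.0 = 7.2).

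**Simulation 2.** 4000 runs, site SD 0.5, unstratified against stratified by disease type. Disease HR 2: 54.4% against 57.0%, a gain of 2.6 points. Disease HR 3: 51.9% against 56.5%, a gain of 4.6. Under no effect at HR 3, the unstratified test rejects in 2.9% of runs and the stratified tests (by disease type, or by disease type and hospital type) in 3.8% to 4.0%.

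**Simulation 3.** Same comparison, same trial size and relapse rates. No gain or cost when the strata are not prognostic (56.0% both ways); about 0.5 points at disease HR 1.5, 1 to 2 at HR 2, and about 4 at HR 3. Unstratified rejection under no effect is 4.2% at HR 2 and 3.1% at HR 3.

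**Disagreement between p-value and interval.** 1500 runs per scenario under 40% against 25%. The plain log-rank test and the adjusted Cox interval gave opposite verdicts on significance in 5.6% of trials with no prognostic covariate. The figure was 6.2% with site SD 0.5 and disease HR 2, and 9.6% when one listed covariate was also prognostic (HR 1.5 per SD).

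**The case against.** The strongest reply is that the article is silent on strata rather than committed to an unstratified test, and that such detail commonly sits in the analysis plan, which is not shown. A log-rank test accompanied by an adjusted Cox hazard ratio is also a common pairing. This stands in part: the plan should not be read as rejecting stratification. But the article itself fixes the test, the source of the hazard ratio and the covariates, and what it fixes does not match its own randomization.

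Several stronger readings are tempting and are not supported:

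- **That power is lost outright.** A reader might infer this from the mismatch. The loss depends on prognostic strength that the article does not give, and with weak strata there is none.
- **That disease type is ignored.** The Cox model names it and an interaction test is planned. Site is the stratum named in neither the test nor the model.
- **That the two descriptions of the strata cost power, or flatly exclude each other.** The Trial design section is less complete and does not deny stratification by disease type. The mismatch has no power effect of its own.
- **That false positives increase.** In every scenario the plain test stays at or below 5% within simulation error.

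**Conclusion.** The point holds in a limited form. The primary p-value and the interval for the hazard ratio rest on different adjustments, neither as stated uses both randomization strata, and they can give conflicting answers. The conflict rate is roughly 6% to 10% of trials under the assumed covariate strengths.

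The cost of leaving disease type out of the test is about 0 to 0.5 power points at a disease-type hazard ratio of 1 to 1.5, 1 to 3 points at 2 and 4 to 5 points at 3, with a conservative test at the upper end. These sizes rest on 40% against 25% relapse, a 40% ulcerative colitis share and assumed strengths for site and disease type. The effect is small beside the separate question of whether 90 per group is enough. The change is worth making because it is nearly free and removes an ambiguity about the primary result.

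**What to change.** 1. State that the primary log-rank test is stratified by disease type. Do not stratify it by all 20 site-by-disease cells. Tertiary against general hospital is not needed either: it is not a randomization stratum and adding it changed power by less than 1 point.
2. Take the primary hazard ratio and its 95% confidence interval from a Cox model with the same stratification.
3. Account for site in that Cox model in a way that copes with small centers, for example a shared frailty, or do so as a sensitivity analysis.
4. Keep the multi-covariate Cox model as supportive.
5. Align Trial design with Randomization and masking so that both give the strata actually used.

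The cost is wording in the protocol and analysis plan. No extra patients or data are needed, since site and disease type are already recorded. The change should be fixed before relapse is compared by arm.

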**Fig. 3 Fig3:**
[figure not shown]
IBD-live schedule of enrollment, interventions, and assessments. Comparability between groups will be assessed by summarizing emotional maturity (Bar-On EQI:JV), quality of life (IMPACT-III), and drug adherence (Morisky Medication Adherence Scale, MMAS). All of these questionnaires will be completed at home within one week after enrollment

The outcome parameter of the economic evaluation is the number of relapses within one year. With this outcome parameter, the incremental cost-effectiveness ratio provides information to guide preference of the web-assisted calprotectin-based treatment algorithm over usual care. The time horizon of the evaluation will be from randomization to the end of the study. Uncertainty surrounding cost-effectiveness ratio will be explored by bootstrap replication and by varying the major cost components. Discounting will *not* be applied. The economic evaluation will be performed from a societal perspective, incorporating costs of travel to the hospital and costs of leave from work of the parents, as well as direct medical costs of IBD care (costs of medication, outpatient visits). Questionnaires will be used to collect data regarding health care consumption, travel and time costs and productivity loss at study entry and at one-month intervals thereafter. Other relevant data regarding health care consumption such as number of contacts or visits with the local IBD team, unscheduled health visits, hospital admissions, and drug use will be recorded or collected from existing hospital databases. Unit prices will be determined according to Dutch guidelines. Standard prices will be used if available and applicable, according to the type of hospital where the patient is treated. Productivity loss will be calculated using the friction cost method. The IMPACT-III score will be used in the patient outcome analysis and provides an estimate of the relationship between the difference in quality of life and the difference in costs of both treatments. At the end of the observation period we will evaluate the teenagers and caretakers in the intervention group for their attitude towards E-health.

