### Participant timeline

Teenagers who are potentially eligible based on inclusion criteria will be identified and informed about the trial by the local IBD team. In case the teenager is interested in participation an information pack will be sent by mail, containing a patient invitation letter, a participant information sheet and consent forms. Patients who do not participate due to exclusion criteria or refusal will be anonymously recorded, including patient characteristics and, if available, the reason for non-participation.

During the outpatient appointment the health provider will (1) recheck whether the participant has daily access to a smartphone or tablet or an internet connection, (2) assess whether the last relapse was more than three months before, and (3) identify parents or legal guardians. After written informed consent has been obtained, but before randomization occurs, each patient will undergo a detailed assessment (Fig. 3). Data collected will include demographic information (including travel time to clinic, level of education of both patient and parents), clinical and IBD-specific history (including age at diagnosis, type of IBD, disease location, date of last relapse and current maintenance treatment). The (pediatric) gastroenterologist will perform a general physical examination (including measurements of height and weight, and assessment of pubertal maturation) and will rate the current disease activity by using the PCDAI or PUCAI.

Irrespective of group assignment, each participant will be evaluated at the local trial site at six and twelve months for disease activity (by physician rated PUCAI or PCDAI), serological markers of inflammation and fCal. Each participant will complete a diary for school-absenteeism and parental absence from work once every month, and IMPACT-III and MMAS questionnaires at six and twelve months. Reminders will be sent by email, with a direct link to the online questionnaires.

In between scheduled health visits teenagers assigned to the experimental group receive alerts to use the online flarometer and to send a feces sample by pre stamped return envelope for fCal rapid analysis. Teenagers assigned to usual care may have outpatient appointments at three and nine months, depending on the health check interval prior to participation.

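### Free improvement: compare 12-month IMPACT-III adjusted for its baseline value, instead of testing the change score

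*Protocol article*

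**What the plan says.** Study objectives postulates higher IMPACT-III scores among IBD-live users. Outcomes places the score among the secondary endpoints: "We are collecting data from a range of secondary endpoints, including the IMPACT-III score". The same section fixes the comparison. The quantity is given by "To compare the difference of IMPACT-scores from baseline to final visit", and for the method Student's t-test or "analysis of variance will be used where appropriate".

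No section names baseline IMPACT-III as a covariate. Other study parameters promises emotional maturity and education as covariables in the final analyses, without saying which analyses. Participant timeline has every participant complete "IMPACT-III and MMAS questionnaires at six and twelve months". The six-month score has no role in the comparison described under Outcomes.

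Three places bear on when the baseline questionnaires are filled in. The Fig. 3 legend, on emotional maturity, IMPACT-III and drug adherence, says: "All of these questionnaires will be completed at home within one week after enrollment". Participant timeline says that after consent, "but before randomization occurs, each patient will undergo a detailed assessment", and refers to Fig. 3. Randomization and masking has the website withhold the code until the teenager is recruited, "which takes place after all baseline measurements have been completed".

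**The concern.** With two arms and two time points, a t-test on change, a one-way analysis of variance on change, and the arm-by-time term of a repeated-measures analysis of variance are the same test. So whichever option is judged appropriate, the comparison is of mean change unless a covariate is added.

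A change score takes the baseline into account by subtracting it in full. That is the best use of the baseline only if r is 1. For any smaller r it over-corrects: part of the baseline's random variation is carried into the outcome, and an arm that happens to start higher tends to look worse at the end. ANCOVA estimates the slope and avoids both problems. At stake is precision on a named hypothesis, in a trial that gives no separate sample-size reasoning for this endpoint.

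The timing wording matters because the trial is open label and the questionnaires are self-reported. The argument that the change score is unbiased needs a baseline completed before allocation is known.

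**Working it through.** **Inputs.** Sample size gives 90 patients per group, allowing for at most 10% loss, so 90 × 0.9 = 81 evaluable per group. Allocation is 1:1. The article states no standard deviation, target difference, power or correlation for IMPACT-III, so there is no figure of its own to reproduce. I set the SD to 1, take r as an assumption from 0.3 to 0.8, and use two-sided 5% and 80% power, the levels stated for the primary endpoint.

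**Variance per patient.** Change score: 2(1 − r). Baseline-adjusted: 1 − r². Ratio: (1 − r²) / [2(1 − r)] = (1 + r)/2.

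**Detectable difference** with variance v: (1.960 + 0.842) × √(2v/81), in SD units. The last column is the power of ANCOVA at the difference for which the change score has 80%.

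| r (assumed) | Change variance | ANCOVA variance | Ratio | Detectable, change | Detectable, ANCOVA | ANCOVA power |
|---|---|---|---|---|---|---|
| 0.3 | 1.40 | 0.91 | 0.65 | 0.52 | 0.42 | 93.5% |
| 0.4 | 1.20 | 0.84 | 0.70 | 0.48 | 0.40 | 91.8% |
| 0.5 | 1.00 | 0.75 | 0.75 | 0.44 | 0.38 | 89.9% |
| 0.7 | 0.60 | 0.51 | 0.85 | 0.34 | 0.31 | 86.0% |
| 0.8 | 0.40 | 0.36 | 0.90 | 0.28 | 0.26 | 84.0% |

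For r of 0.4 to 0.7 the variance falls by 30% to 15%. The confidence interval narrows by 1 − √0.70 = 16% to 1 − √0.85 = 8%. That is worth 1/0.70 = 1.43 to 1/0.85 = 1.18 times as many patients on this endpoint. Below r = 0.5 the change score is even less precise than comparing 12-month scores with no use of the baseline (variance 1.40 against 1.00 at r = 0.3).

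**Chance imbalance.** If the arms happen to differ by 0.2 SD at baseline, the change-score contrast is off by (1 − r) × 0.2 in that realised trial: 0.14, 0.10 and 0.06 SD for r of 0.3, 0.5 and 0.7. Over repeated randomizations this averages to zero.

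**Six-month score.** With complete data and an unrestricted covariance, the 12-month contrast from a mixed model is essentially the 12-month ANCOVA. The six-month score adds information mainly for patients lost before 12 months, projected at no more than 10%.

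**Timing.** If enrollment means consent, the three places fit together: consent, questionnaires at home within a week, then release of the code. Harms links enrollment with consent, which favours this reading. If enrollment means recruitment in the sense used under Randomization and masking, the Fig. 3 legend and that section conflict. The items listed under Participant timeline do not include the three questionnaires, and Fig. 3 itself is not available here, so the text alone does not settle the order.

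**The case against.** The strongest reply is that nothing here is an error. The change score uses the baseline, it is unbiased under randomization, and the endpoint is secondary. The exact model is commonly left to an analysis plan that is not shown, and the wording under Outcomes together with the promised covariables leaves room for adjustment. Most of this stands, and it is why the point is an improvement and not a fault in validity. But the article does name a specific comparison, and the covariables that it names do not include baseline IMPACT-III.

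It is also fair that the gain rests on an assumed r. At r = 0.8 the variance saving is only 10%. Nor should the six-month score be called wasted: the patient outcome analysis in the economic evaluation uses IMPACT-III without restricting the time points, and multiple imputation is already planned for random missing data.

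A reader might infer from the Fig. 3 legend that the baseline questionnaires are filled in after the allocation is known, which would bias the change score and affect emotional maturity as a covariate in the Cox model. The document does not support that. Randomization and masking holds back the code until all baseline measurements are done, Participant timeline puts the detailed assessment before randomization, and the legend says enrollment, not randomization. No section says that enrollment and randomization share a visit.

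**Conclusion.** The point holds as a free improvement. The planned IMPACT-III comparison is valid if the baseline precedes allocation, but it is less efficient than adjusting for a baseline that the trial already collects. The large-sample variance reduction is 35% to 10% for r of 0.3 to 0.8. These figures assume equal variances at the two time points and a linear relation to baseline; r itself is not in the document. Two further readings do not hold: the plan does not ignore the baseline, and there is no evidence of a baseline contaminated by knowledge of the allocation. On timing, only wording needs to be reconciled.

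**What to change.** Replace the sentence under Outcomes with a comparison of the 12-month IMPACT-III score between arms, adjusted for baseline IMPACT-III and for site and disease type, the strata named under Randomization and masking. Either of two forms will do:

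- an ANCOVA at 12 months; or
- a mixed model on the six- and 12-month scores with visit and visit-by-arm terms, the 12-month contrast being pre-stated as the test. This form also uses the six-month scores of patients lost later.

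Separately, amend the Fig. 3 legend to say that the three baseline questionnaires are completed before the randomization code is released, and use one meaning of enrollment there, under Participant timeline and under Randomization and masking.

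The cost is wording. No new data are needed. Any wait for the home questionnaires before code release is already implied by Randomization and masking.
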